Breast cancer is strongly influenced by female sex hormones such as oestrogen and progesterone; both by those produced naturally in a woman's body (endogenous hormones), and by hormones taken for contraception or as hormone therapy for the menopause (HT) (exogenous hormones). Current users of both hormonal contraceptives and HT have an increased risk of breast cancer, up to 2-fold in the case of HT preparations containing both oestrogen and a progestagen (synthetic progesterone). Understanding these risks has direct implications for public health: for example, rates of breast cancer have fallen in response to falls in prescribing of HT, following publication of reliable evidence on breast cancer risk in recent years. There are however some gaps in our knowledge. It has been suggested that the effect of HT on breast cancer risk may depend on the timing of use (in relation to age or menopausal status); and there is limited information on the risks associated with progestagen-only contraceptives, or with specific contraceptive formulations. The GPRD's large size and the availability of detailed prescription data by type will allow us to examine these questions; our analyses would extend and supplement previous GPRD studies of hormone use and breast cancer.

Objectives, specific aims and rationale

*Research objective:* to obtain relative risks for incident breast cancer in relation to prior prescribing of contraceptive hormones and of hormone replacement therapy for the menopause (HT), by type and timing of use.

*Specific aims:* to add to existing knowledge about the effect of use of exogenous female sex hormones on risk of breast cancer, examining unanswered questions including the influence on risk of the timing of HT use, and suggested differences in risk associated with specific contraceptive preparations.

*Rationale:* current use of both HT and contraceptive hormones has been shown to increase risk of breast cancer, and this knowledge has direct public health implications. The large size and reliable prescribing information in the GPRD will allow us to add to existing knowledge by examining breast cancer risk in relation to specific hormone preparations and to timing of HT use, where there is at present suggestive but unconfirmed evidence for differences in risk.

Background

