The development of breast cancer in women is strongly influenced by female sex hormones, and the risks associated with reproductive patterns (parity, age at first birth) and with use of oral contraceptives and of hormone therapy for the menopause have been extensively described [1-6]. However, unanswered questions remain. For hormonal contraceptives, there is good evidence for a modest increase in risk of breast cancer in current users of oral contraceptives containing both oestrogen and progestagen, both for older [4] and more recent [7] preparations, with relative risks for current compared with never use of around 1.3. There may be higher risks associated with specific formulations and modes of delivery, such as triphasic pills containing levonorgestrel [7], but evidence is limited. Similarly the risks associated with use of progestagen-only contraceptives, including the intra-uterine device Mirena, are not clear [4].

Some types at least of hormone therapy for the menopause are known to be associated with increased risk of breast cancer, with relative risks of about 2 reported for current use of combined oestrogen-progestagen preparations [8]. It has recently been suggested that the effect of HT use on breast cancer risk may vary depending on women's age and/or menopausal status when use starts, with risk higher for use starting around the time of the menopause than for later use [9]. Such findings have important potential implications for clinical practice and need to be investigated in independent datasets. There is debate too about the relative risks associated with different formulations of HT, including, again, the use of Mirena progestagen-releasing intrauterine devices [10]; as well as differences by mode of drug delivery (transdermal vs oral) [11].

We are not aware of previous research studies in the GPRD examining cancer risk in relation to use of hormonal contraceptives. For HT, five previous publications have described analyses of HT use and risk of breast cancer from the GPRD [12-15]. The most comprehensive, with 6,347 cases aged 50-75 [14], used data up to 2004; the most recent (1261 cases with data to 2007) focussed on risk associated with a specific progestagen, dydrogesterone [15]. Our proposal would allow updating and extension of the previous analyses to 2010, to include all HT types, including Mirena, and to examine risk by timing of use.

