Reliable analyses by hormone type require large numbers of exposed cases, as well as detailed prospective information on prescribing. The GPRD has both, and sufficient information to allow adjustment or stratification by known potential confounders such as body mass index and alcohol use (as well as some less well-established risk factors for breast cancer such as smoking and use of aspirin).

Finally, a major source of evidence on the effects of exogenous sex hormones on breast cancer risk has been, and will continue to be, the results from pooled reanalyses of individual data included in the international Collaborative Group on Hormonal Factors in Breast Cancer mentioned above. The proposers of the current study also run this collaboration; collaborative results are currently being updated for both hormonal contraceptives and for hormone therapy for the menopause, and a comprehensive and up to date analysis of GPRD data would allow the optimal contribution from GPRD to the worldwide evidence.

Study type

Hypothesis testing and confirmation of findings of public health significance.

Study design

Nested case-control study within defined cohort in GPRD, using cases and controls matched for age, practice and observation time in the GPRD. 2 controls will be selected per case to maximise study power.

Study population

Women aged 20-79 years registered with GPRD on or after 1 January 1995.

Inclusion criteria:

- Age 20-79 [age group includes almost all cancers and hormone prescriptions]
- Registered with GPRD up –to-standard practice on or after 1 January 1995
- Fulfilling GPRD acceptable patient criteria
- At least 1 year in GPRD before index date (date of diagnosis of case)

Exclusion criteria:

- Previous invasive or *in situ* breast cancer

Case selection

Cases will be identified as any eligible patient with an incident diagnosis of invasive or *in situ* cancer of the breast between 1 January 1995 and latest available date.

Selection of comparison group (controls)

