2 controls per case selected from eligible patients who do not have a medical diagnosis of breast cancer documented at any time up to the latest available date (above). This includes diagnoses of breast cancer prior to or during the study period. Controls and cases matched on age (within 2 years), practice and observation time in GPRD (ie controls to have observation time in GPRD at least as long as their matched case, to allow exact matching in the analysis; for cases, start date of observation = most recent of patient registration date, practice up-to-standard date and practice management start date, end date (index date) = date of diagnosis). Index date for controls defined as the diagnosis date of their matched case.

Sample size and power calculations

Incidence of invasive breast cancer in GPRD is similar to that in the general UK population, which is ~63 per 100,000 per year (Office for National Statistics (ONS), 2007) ie 630 cases per million person years. There are currently 62 million person years of research acceptable followup in GPRD (GPRD Gold October 2010 release), so we might expect some 39,000 incident breast cancers in the whole database, and of these about 20,000 will be in women aged 50-75 (ONS, 2007). It seems reasonable to assume, allowing for some restriction of age group and observation time, that our analyses would include at least 10,000 breast cancer cases and 40,000 controls. These numbers are consistent with those in the GPRD study by Opatrny et al, which included incident cases of invasive breast cancer in women aged 50-75 diagnosed between 1998 and 2004, and had over 6,000 cases [14]. From the Opatrny study and from our previous analyses in GPRD (protocol no. 10_006; analyses not yet published) the prevalence of HT prescribing in women over 40 years will be approximately 33 % (possibly lower in very recent years); OC prescribing in women 20-50 years is estimated at about 20 % in GPRD in recent studies of outcomes other than cancer [16].

With these numbers the study will be amply powered with 80% power and 95% confidence to detect a minimum relative risk of <1.1 in relation to overall risk for HT or OC use v no use, and of <=1.5 for any subgroup with exposure prevalence of 1% or more.

Exposures, outcomes, covariates

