Exposure: patients will be considered exposed to exogenous hormones if they have at least one prescription for a hormonal contraceptive or hormone replacement therapy preparation (as defined in the British National Formulary (BNF)) within the observation period (start of follow-up to index date). Sensitivity analyses will be performed restricting the definition of exposure to those with 2 or more prescriptions. OC/HT type will be assigned based on BNF classification, classing women with separate prescriptions on the same day for oestrogen and progestagen as being prescribed combined oestrogen-progestagen therapy.

Outcomes: incident invasive and *in situ* cancers of the breast (ICD-10 C50 and D05)

Covariates: smoking status, alcohol drinking [most recent record before index date], body mass index [most recent record at least 2 years before index date, to account for reverse causality] and parity will be taken into account where possible in adjusted and/or stratified analyses. Availability of prescription data will allow medications such as aspirin and bisphosphonates, which may be related to breast cancer risk and to hormone use, to be considered in supplementary analyses.

Data/statistical analysis outline methodology

Conditional logistic regression will be used to estimate crude and adjusted odds ratios (relative risks) with 95% confidence intervals for cancer risk in relation to hormone prescription vs no prescription within the observation period. Analyses for hormonal contraceptives will include hormone type and mode of delivery, including progestagen-only contraception; for HT, hormone type, mode of delivery and timing of use; for both, the risks associated with use of Mirena will be examined. Adjustment variables will include smoking status (never, current, past, unknown), alcohol drinking (none, some, unknown) and body mass index (<25, 25-30, 30+ kg/m sq, unknown) and where possible, parity (at least nulliparous, parous, unknown). Data analysis will be carried out using STATA software v10. Analyses for HT will generally be restricted to women aged over 40, and for OC use to women aged 20-50 years.

Patient/user group involvement

None

Limitations of study design, data sources, analytic methods

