**Revised definitions of cases and controls**

In keeping with the above protocol, the revised definitions for cases and controls are outlined as follows. All women are required to have a minimum of 12 months up-to-standard data in the CPRD prior to index date (date of diagnosis for the case) to be eligible for study inclusion.

Case definition

Cases are defined as all female participants of the CPRD with incident diagnosis of invasive or in situ breast cancer documented between 1^st^ January 1995 and 2017 (to most recent data available), and aged 20- 79 years of age at index diagnosis. Women are excluded if they have a past history of invasive or in situ breast cancer.

The list of Read codes used to flag women with incident breast cancer diagnosis as per previous protocol is shown Appendix 1.

Control definition

Controls are defined as all women without a medical diagnosis of breast cancer documented (up to last date of data extraction for 2017). This includes any diagnoses for breast cancer prior to 1^st^ Jan 1995 and during the study period from 1^st^ Jan 1995 to 2017. Cases are therefore not eligible to act as controls in this study.

Controls will be matched in a 2:1 ratio to cases based on:

- Year of birth(+/- 2 years)
- Same general practice
- Similar period of observation as the case.

The period of observation in CPRD for controls must include the full observation time (regstart to index diagnosis) for cases, so that observation periods may be matched exactly for the purpose of analyses.

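### The early-versus-late HT start comparison is weakened because start is dated only inside a left-truncated window, with no HT-free run-in to separate new starts from continuing use

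*Protocol*

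**What the plan says.** Under Objectives, specific aims and rationale, the protocol commits to "examining unanswered questions including the influence on risk of the timing of HT use". The lay summary explains timing as an effect that "may depend on the timing of use (in relation to age or menopausal status"). The Background gives the direction of the hypothesis: "with risk higher for use starting around the time of the menopause than for later use". The study type is hypothesis testing.

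The analysis outline then names the HT analyses as "for HT, hormone type, mode of delivery and timing of use", without saying how a start is dated. What is fixed is the exposure window. Under Exposures, outcomes, covariates, a woman is exposed if she has at least one relevant prescription "within the observation period (start of follow-up to index date"). The section on controls sets the opening of that window for cases: "start date of observation = most recent of patient registration date, practice up-to-standard date and practice management start date". The 2017 amendment keeps the minimum length: "All women are required to have a minimum of 12 months up-to-standard data in the CPRD prior to index date".

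The covariates are smoking, alcohol, body mass index and, where possible, parity, with some other medicines in supplementary analyses. Menopausal status, hysterectomy and oophorectomy are not named. The limitations section mentions incomplete lifestyle and reproductive data and contraceptive prescriptions issued outside general practice. It concludes that such gaps cost power but should cause no bias so long as they are unrelated to outcome. It does not mention HT use before the window opens.

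**The concern.** The timing hypothesis needs the date at which HT began. The protocol's window shows the date of the first prescription after the practice record becomes usable. The two agree for a woman who starts HT while under observation. They differ for a woman who enters already on treatment, and the protocol has no rule to tell the two apart.

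The error runs one way: the first counted prescription can fall after the true start but never before it. Early starters can therefore move into the late-start group, and late starters cannot move into the early-start group. If early starts do carry the higher risk, the late group's estimate is pulled up and the contrast shrinks. The Background says the timing question has potential implications for clinical practice, so a precise but diluted result could be read as evidence that timing does not matter.

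**Working it through.** **The plan's own figures.** The power section claims a detectable relative risk below 1.1 for HT or contraceptive use against no use, and at most 1.5 for a subgroup with 1% exposure, at 80% power and 95% confidence. Take exposure prevalence p0 in controls and p1 = p0·OR / (1 − p0 + p0·OR) in cases, with a two-sided 0.05 test of two proportions that ignores the matching:

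| Cases : controls | p0 = 33% | p0 = 20% | p0 = 1% |
|---|---|---|---|
| 10,000 : 40,000 (numbers in the power section) | 1.068 | 1.080 | 1.335 |
| 10,000 : 20,000 (2 controls per case, as in the design) | 1.075 | 1.088 | 1.372 |

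The stated figures hold under either ratio. The overall claim is for use against no use, and no figure is given for early against late start. Power also offers no protection against a contrast that is biased.

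**How a start gets misdated.** Suppose a woman begins HT at 50, registers with the practice at 60 while still taking it, and has an index date at 61.

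- Her window runs from 60 to 61, which meets the 12-month minimum.
- Her first counted prescription is at about 60.
- Dated from the window, her start is about 10 years late and her use appears to have lasted about 1 year.

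Her matched control is viewed over the same window, so a control with the same history is misdated in the same way.

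**Why equal error does not cancel.** Let c be the proportion of control women dated as late starters who really began early. Let RR_E and RR_L be the true relative risks against no use. Expected cases in each part of the apparent late group are proportional to its controls multiplied by its relative risk, so:

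- apparent late RR = (1 − c)·RR_L + c·RR_E
- apparent early/late ratio = RR_E / apparent late RR

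The early group is unaffected because misdating runs one way. This simple model assumes that misdated early starters carry the same relative risk as other early starters, and that misdating is equally likely in cases and controls.

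**Illustration.** RR_E = 2.0, RR_L = 1.5 and the values of c are all assumptions. The Background's value of about 2 is for current combined HT, not for early start.

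| c | Apparent late RR | Early/late ratio | Share of the excess over 1 lost |
|---|---|---|---|
| 0 | 1.500 | 1.33 | none |
| 0.20 | 0.80×1.5 + 0.20×2.0 = 1.600 | 1.25 | 25% |
| 0.35 | 0.65×1.5 + 0.35×2.0 = 1.675 | 1.19 | 42% |
| 0.50 | 0.50×1.5 + 0.50×2.0 = 1.750 | 1.14 | 57% |

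The last column is (1.333 − ratio)/0.333. With a wider assumed gap (RR_L = 1.2), the true ratio of 1.67 falls to 1.43 at c = 0.25 and 1.25 at c = 0.50.

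**Against the limitations section.** In this model nothing depends on case status given the true start, yet the ratio moves towards 1. The assurance that gaps unrelated to outcome only dilute power therefore does not carry over to unseen earlier HT use in this comparison.

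**The case against.** The strongest reply is that this is an outline. How a start is dated, and how women already on HT at entry are handled, are commonly left to an analysis plan, and one may exist that is not shown. The protocol never says that start means first recorded prescription. That is fair, and the absence of such a rule would not be a finding alone. But the protocol does fix the window, its opening and its minimum length, and its general assurance about incomplete data does not hold for this aim.

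A reader might infer that the aim cannot be met at all. The documents do not support that. Twelve months is a minimum, no distribution of window lengths is given, and index dates run from 1995 to 2010, extended to 2017. Nor is a menopause variable indispensable: the lay summary words timing as age or menopausal status, and age is known. Age at start can be studied in women seen to be free of HT first.

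A reader might also infer that early starters are compared with premenopausal non-users because HT analyses begin at about 40. That confuses age at start with age at index. Controls are matched on age and share the case's index date, so a woman who started at 50 and was diagnosed at 62 is compared with women of about 62. The worry is confined to women whose index date falls around or before the usual age of menopause, and it does not describe the early-start group as a whole.

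Finally, exact matching of observation time gives cases and controls the same look-back. That limits differential error but does not recover the true start date.

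**Conclusion.** The point holds in a limited form. As written, the exposure definition does not support the early/late start comparison well: use continuing at entry can pass for a late start, and the resulting dilution does not need the error to differ between cases and controls. The limitations section does not acknowledge it.

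The size cannot be computed from the documents. A fall in the ratio from 1.33 to between 1.25 and 1.14 rests wholly on assumed relative risks and assumed contamination of 20% to 50%, and a loss of more than half the contrast appears only at the top of that range. The direction, towards no difference, depends on early starts truly carrying the higher risk, as hypothesised.

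Timing of HT is one aim among several. This argument does not extend to the contraceptive, HT type or mode-of-delivery analyses. The change should be made, but it does not undermine the study as a whole.

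**What to change.** Restrict the timing analysis to women with a stated HT-free period, at least 12 months of up-to-standard observation, before their first HT prescription, and classify them by age at that prescription. Keep women already on HT at entry for the hormone-type and mode-of-delivery analyses. Where menopause, hysterectomy or oophorectomy codes are recorded, use them to describe start relative to menopause, and report how complete they are.

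In the limitations section, add two items specific to the timing aim: HT use before the window opens is unseen, and menopausal status is incomplete. State there that the assurance about gaps unrelated to outcome does not cover this comparison.

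The cost is small: an analysis definition and a code list applied to the existing extract. The amendment reports that analyses were not finalised and asks for a full dataset refresh, so there was room to do this. The downside is fewer women. An HT user whose whole window is only 12 months cannot show 12 HT-free months before a first prescription, so the shortest windows contribute no new users. A run-in also reduces misdating without removing it: a woman who used HT years earlier, stopped, and restarted under observation would still look like a new starter.

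### HT and contraceptive users are compared with all same-age non-users without regard to menopausal status, which biases HT odds ratios down at about 41-54 and contraceptive odds ratios up near 50; the pooled shift is small and the remedy cheap

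*Protocol*

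**What the plan says.** The section on outline statistical methodology fixes three things.

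- **Contrast:** odds ratios are estimated "for cancer risk in relation to hormone prescription vs no prescription within the observation period".
- **Age ranges:** "Analyses for HT will generally be restricted to women aged over 40, and for OC use to women aged 20-50 years". The two ranges overlap in the forties.
- **Adjustment:** "Adjustment variables will include smoking status (never, current, past, unknown), alcohol drinking (none, some, unknown) and body mass index", plus "where possible, parity (at least nulliparous, parous, unknown".

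The section on selection of controls adds the matching rule: "Controls and cases matched on age (within 2 years), practice and observation time in GPRD".

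Menopausal status, age at menopause, hysterectomy and oophorectomy appear in none of these rules. They are also absent from the limitations section, which does name parity, breastfeeding and age at first birth as poorly recorded. Menopausal status comes up only in the lay summary and background, as something that might modify the HT effect according to when use starts.

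The lay summary also gives the premise that matters here. It says that female hormones strongly influence breast cancer, "both by those produced naturally in a woman's body (endogenous hormones") and by those taken as medication.

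**The concern.** HT is prescribed for the menopause. Among women in their forties and early fifties, those with an HT prescription are therefore more likely to be peri- or postmenopausal than those of the same age without one. On the protocol's own premise, the non-users then carry more hormonal exposure from their own ovaries. Menopausal status is linked to both exposure and outcome. Matching on age cannot balance it, because the imbalance exists among women of the same age. HT odds ratios at these ages are pulled down.

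For contraceptives the imbalance reverses. Users in their late forties are mostly premenopausal, while some non-users have passed the menopause, so the odds ratio is pushed up.

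The study's added value is meant to lie in HT type, mode of delivery and timing, and in contraceptive type. The bias is concentrated in particular ages, so two HT types or two timing groups with different age mixes would be distorted by different amounts. That could create or hide a difference between them.

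**Working it through.** **The plan's own figure.** The sample size section claims 80% power at 95% confidence for a relative risk below 1.1 overall, and of 1.5 or less at 1% exposure prevalence. For 10,000 cases and 40,000 controls, an unmatched two-proportion calculation (two-sided 0.05) gives minimum detectable odds ratios of 1.068 (HT, 33% exposed), 1.080 (contraceptives, 20%) and 1.33 (1%). With the two controls per case of the design section they are 1.075, 1.088 and 1.37. The power claim holds. It serves here only as a scale for the bias.

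**Bias within an age band.** Let *r* be the risk ratio of premenopausal to postmenopausal women of the same age, and *p*_u and *p*_n the premenopausal shares of users and non-users. The odds ratio is multiplied by

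[1 + *p*_u(*r* − 1)] / [1 + *p*_n(*r* − 1)].

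The documents give none of these inputs; all are assumptions. Results for *r* = 1.4, with the range for *r* = 1.7 to 1.2:

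| Analysis and age | *p*_n | *p*_u | Factor at *r* = 1.4 | Range |
|---|---|---|---|---|
| HT 41-45 | 0.90 | 0.20 | 1.08/1.36 = 0.79 | 0.70-0.88 |
| HT 46-50 | 0.65 | 0.15 | 1.06/1.26 = 0.84 | 0.76-0.91 |
| HT 51-55 | 0.20 | 0.05 | 1.02/1.08 = 0.94 | 0.91-0.97 |
| HT 56+ | 0.03 | 0 | 1/1.012 = 0.99 | 0.98-0.99 |
| Contraceptives 46-50 | 0.65 | 0.95 | 1.38/1.26 = 1.10 | 1.05-1.14 |

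At *r* = 1.4, a true HT odds ratio of 2.0 (about what the background cites for current combined use) reads 1.59 at 41-45 and 1.68 at 46-50. A contraceptive odds ratio of 1.3 (also from the background) reads 1.42 at 46-50, range 1.37-1.49.

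**A second set of assumptions.** Take all HT users as postmenopausal, so the factor is 1/[1 + *p*_n(*r* − 1)], with *r* from 1.2 to 1.6:

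- *p*_n = 0.95 (about 40-44): 0.84 to 0.64
- *p*_n = 0.75 (about 45-49): 0.87 to 0.69
- *p*_n = 0.30 (about 50-54): 0.94 to 0.85

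For contraceptives, with all users premenopausal and 25% of non-users postmenopausal, 1.3 reads 1.3/(0.75 + 0.25/*r*) = 1.36 to 1.43.

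**Pooled estimates.** Using the second set:

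- HT at 40-79. Assumed case shares of 6, 10, 14 and 70% at 40-44, 45-49, 50-54 and 55-79, with HT prevalence of 5, 15, 35 and 38%, give information weights of 1.3, 6.0, 15.0 and 77.7%. *p*_n is taken as 0 at 55-79. The weighted mean of the log factors gives 0.98 (*r* = 1.2), 0.96 (1.4) and 0.95 (1.6), so 2.0 reads 1.96 to 1.90.
- Contraceptives at 20-50. Assumed case shares of 25, 30 and 45% in three successive age groups, contraceptive prevalence of 35, 18 and 8%, and premenopausal shares of 100, 95 and 75% among non-users make 1.3 read 1.32 to 1.34, a rise of about 1-3%.

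Putting the table's HT factors through assumed weights of 5, 10, 17 and 68% gives 0.98, 0.95 and 0.93 for *r* = 1.2, 1.4 and 1.7. The pooled HT shift therefore reaches about 7% only at the top of the assumed range.

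**On the scale of the power claim.** A true HT odds ratio of 1.07, multiplied by 0.95-0.98, reads about 1.02-1.05. A larger sample does not reduce this.

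**The case against.** The strongest objections are these.

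- **The size is assumed.** The documents give neither the risk ratio nor any premenopausal share. Perimenopausal HT users keep some ovarian function, and use that starts before the menopause would weaken the contrast. This stands: the protocol's premise supports the direction, not a particular figure.
- **The headline barely moves.** This also stands. A reader might infer from the results at 41-50 that a real HT excess could disappear or reverse in the main result. Some illustrative values do this within that decade: a true 1.2 reads 0.95 at 41-45 with *r* = 1.4. The pooled shift is far smaller, and nothing in the documents suggests a reversed headline.
- **The text leaves room.** The age sentence is qualified by the word generally, timing analyses are planned, and an analysis plan not shown here might define menopausal status or age strata. That is fair for the detail. The contrast, age ranges and covariates are nevertheless set out in the protocol, and none uses menopausal status. The limitations section omits it too.
- **Moving the age ranges is no clean cure.** A reader might conclude that the main HT analysis must start at 50, because the sample size section cites a GPRD study "which included incident cases of invasive breast cancer in women aged 50-75". That study is cited there for case numbers and HT prevalence, not as a design template, and the protocol sets out to extend earlier work. Starting at 50 would leave a factor of about 0.94 at 51-55 and would drop early users, who matter for the timing aim. Ending the contraceptive analysis at 44 would cost cases that the documents do not let one count.

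**Conclusion.** The point holds as a cheap improvement. As specified, HT odds ratios at about 41-54 are biased downwards and contraceptive odds ratios near 50 upwards, because users and non-users of the same age differ in menopausal status and no stated rule handles it. The direction follows from the protocol's own premise about a woman's own hormones and from what HT is prescribed for.

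The size rests wholly on assumed inputs. It is material below 50 and modest at 51-55. In the pooled estimates it is a matter of a few per cent. The practical consequence lies in comparisons of HT type, mode and timing, where groups with different age mixes are shifted unequally.

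The documents do not support the claims that the overall HT result is invalid, that the power statement is wrong, or that either main age range must be replaced.

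**What to change.** Keep the stated age ranges and add three things.

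1. **HT.** Report odds ratios (overall, by type, mode of delivery and timing) by age of the case at index: 41-49, 50-54 and 55-79. Pre-specify a sensitivity analysis at 55-79, or in women postmenopausal by recorded status or a stated age proxy. Base conclusions on type and timing on estimates that agree with it.
2. **Contraceptives.** Report odds ratios separately for ages 20-44 and 45-50.
3. **Limitations section.** Name menopausal status, with the expected direction of bias for each hormone class.

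The age bands do not remove the bias at 41-54. They show where it sits and provide an estimate largely free of it for comparison.

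The cost is a little more analysis and wider intervals in the restricted strata. If 77.7% of the HT information lies at 55-79, as assumed above, the standard error there rises by a factor of 1/√0.777 = 1.13. No new data are needed: the 2017 amendment reports 33,000 cases in the original dataset alone, under eligibility at ages 20-79, although it gives no breakdown by age.
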